#### Randomization and Recruitment Stop

Block randomization will be used, where each participant will be randomly assigned to one of two equally sized, predetermined blocks. Randomization is performed using the respective function provided by the survey platform formr (Arslan et al., 2020) used in this online study. Recruitment will stop if either of the following two criteria is met: (a) The number of recruited participants, i.e. participants who have completed at least the baseline questionnaires and have been randomized, has reached *N* = 192 or (b) the number of complete observations, i.e. datasets containing measurements for all four sessions and follow-up, has reached *N* = 140. As a compensation for taking part in the study, participants will receive a 25 € online retailer voucher.

#### Intervention: Imagery BA

##### Session Content

The present study’s intervention consists of four sessions. In Session 1 (duration approximately 20 minutes), participants are familiarized with information about prevalence and symptoms of depression, the general rationale of CBT and, more specifically, of BA. At the end of Session 1, and following standard BA procedures (e.g., Addis & Martell, 2004), participants are instructed to monitor the kind of activities they engage in and how these activities influence their mood during the following week. To this end, participants receive email invitations to complete an activity monitoring form (for details, see below) at 6 pm on Day 3 and Day 5 after completion of the first session. During Session 2 (duration approximately 25 minutes), participants will receive short, standardized, constructive written and personalized graphical feedback on their activity monitoring forms. Next, to facilitate the identification of idiosyncratic and meaningful activities, participants will be asked to identify three meaningful life areas from a list (see Appendix), rank these based on personal significance, and nominate personal values pertaining to each of these areas. Participants will be instructed to choose two activities they would like to engage in over the following week from their highest-ranked life area. In preparation for the following mental imagery tasks, participants complete a standard imagery training exercise (see paragraph ‘imagery training’ below). Participants then proceed to schedule a time and date within the following seven days for each previously chosen activity. Importantly, and differing from standard BA procedures, participants complete a guided mental imagery task presented via audio recording in which participants are instructed to simulate engagement in the respective activity (for further details, see paragraph ‘imagery-enhanced activity scheduling’ below). In Session 3 (duration approximately 35 minutes), participants fill out activity monitoring forms corresponding to their activities scheduled in Session 2 and receive standardized, constructive written and personalized graphical feedback on this. Next, participants choose three activities (+1 compared to Session 2) and once again complete imagery-enhanced activity scheduling for each of these activities. While participants are encouraged to try out new activities, previously chosen activities may also be re-scheduled. In Session 4 (duration approximately 20 minutes), following completion of activity monitoring forms and having received feedback on these, the intervention concludes with a summary of the study’s rationale. Participants are encouraged to continue planning positive activities and are reminded of the follow-up assessment two weeks later.

##### Study Format

Throughout all sessions, content materials are presented on interactive slides using text, pictures, and audio recordings. Apart from the telephone screening interview, the present study is conducted completely online and unguided. However, participants are encouraged to contact the study team if questions or problems related to the study arise. Participant adherence is encouraged through personalized graphical feedback on activity completion, reminder messages, and individualization (focus on idiosyncratic values). Furthermore, the study team continuously monitors participants’ progress and will contact individual participants if necessary. The current version of the intervention incorporates adaptations made in response to participant feedback received in a pilot trial. For a graphical overview of the study’s procedure, see Figure 1.

**Figure 1 f1:**
[figure not shown]
Procedure *Note.* BADS = Behavioral Activation for Depression Scale (Kanter et al., 2007); BDI-II = Beck Depression Inventory (Beck et al., 1996); CBAS = Cognitive Behavioral Avoidance Scale (Röthlin et al., 2010); FRIS = Freiburg Reward Imagery Scale (https://osf.io/9y64q); Mini-DIPS = Diagnostic Short-Interview for Mental Disorders (Margraf et al., 2017); SUIS = Spontaneous Use of Imagery Scale (Kosslyn et al., 1998); TEPS = Temporal Experience of Pleasure Scale (Gard et al., 2006); WEMWBS = Warwick-Edinburgh Mental Wellbeing Scales (Tennant et al., 2007).

##### Imagery-Enhanced Activity Scheduling

In the present study, standard BA activity scheduling is enhanced by adding a guided mental imagery task, in which participants are instructed to generate emotionally rich, multisensory mental imagery of how they engage in their previously chosen rewarding activity. Participants are guided through the consecutive stages of initiating, engaging in, and completing the activity. Throughout the latter two stages, emphasis is placed on experiencing the positive emotional impact of the activity. Finally, participants are instructed to create a ‘mental snapshot’ of the positive emotional consequences attributed to the activity. The standardized script used in the present study was based on previous studies (Heise et al., 2022; Renner et al., 2019), adapted to the requirements of the present online study format, and pilot-tested. The audio recordings used for the guided imagery task last 2:51 min (female voice) and 2:46 min (male voice) respectively.

##### Imagery Training

Prior to engaging in the imagery-enhanced activity scheduling for the first time, participants in the Imagery BA condition will complete a standard imagery training task (cf. Holmes & Mathews, 2005). In this training task, participants are instructed to generate vivid, first-person mental imagery while making use of all sensory modalities (vision, sound, smell, and so forth). The audio recordings used for the imagery training last 2:35 min (female voice) and 3:00 min (male voice) respectively.

#### Wait-List Control Condition

For participants in the wait-list control condition, the number and frequency of sessions is identical to those of participants in the Imagery BA condition. However, session contents are restricted to the collection of questionnaire data only. Participants in the wait-list control condition can choose to complete the Imagery BA intervention starting one day after the follow-up assessment.

### Materials

The present study has been implemented on the formr platform (Arslan et al., 2020). This online survey platform will be used to collect questionnaire data, perform block randomization of participants, distribute the audio-visual session contents (including guided imagery scripts) to participants, send out email invitations, and reminder messages. To take part in this study, participants require access to a digital device with internet access and the ability to playback audio files (e.g., smartphone, tablet, or laptop).

### Measures

#### Primary Outcomes

##### Behavioral Activation

Behavioral activation will be assessed weekly from baseline (Session 1) to Session 4, and at two-week follow-up using the Behavioral Activation for Depression Scale (BADS; Kanter et al., 2007; German version: Teismann et al., 2016). The BADS conceptualizes behavioral activation as comprising four distinct factors (activation, avoidance/rumination, work/school impairment, social impairment) measured by asking respondents to indicate agreement with 25 statements (e.g., “I did something that was hard to do but it was worth it.”) on a seven-point scale ranging from 0 “not at all” to 6 “completely”. Reliability and validity of the BADS have been supported (Teismann et al., 2016).

##### Depressive Symptoms

Depressive symptoms will be assessed at baseline (Session 1), Session 4, and at two-week follow-up using the Beck Depression Inventory-II (BDI-II; Beck et al., 1996). The BDI-II measures depressive symptom severity across 21 symptoms by letting respondents choose from four (for two symptoms, seven) statements (e.g., “I blame myself all the time for my faults.”) ranked by increasing severity (scoring 0-3 points per symptom). Total scores can range from 0 to 63, with 0-13 indicating minimal depression, 14-19 mild depression, 20-28 moderate depression, and 29-63 severe depression. Reliability and validity of the BDI-II are well supported (Kühner et al., 2007; Wang & Gorenstein, 2013).

#### Secondary Outcomes

##### Acceptability and Feasibility

Acceptability and feasibility of the newly developed online imagery BA intervention tested in this study will be measured by dropout rate during the intervention and by a number of questions on acceptability and feasibility (e.g., “I liked the online format of the study”, “I found it difficult/unpleasant to engage with the study.”, “I would recommend the training to friends”). Responses will be recorded on seven-point Likert scales with end points labelled 0 “not at all” and 6 “very much” and will be obtained at follow-up or – in the case of drop-out – via an additional questionnaire sent to dropped-out participants. Furthermore, open-ended questions are included to encourage participant feedback on this newly developed intervention.

##### Monitoring of Potential Adverse Effects

Potential adverse effects of the intervention will be assessed in terms of symptom deterioration (BDI-II) as well as through questions on acceptability and feasibility. To minimize the occurrence of adverse effects such as suicidal thoughts and behaviors, extra care is taken to identify persons at risk during the screening procedures and intake telephone interview (for details see inclusion criteria in the Participants section above). In addition, a safety protocol to deal with suicidal ideation that includes consultation with a clinical psychologist has been implemented.

##### Mental Well-Being

Mental well-being will be assessed at baseline, Session 4, and follow-up using the Warwick-Edinburgh Mental Wellbeing Scales (WEMWBS; Tennant et al., 2007; German version: Lang & Bachinger, 2017). Respondents rate frequency of occurrence for 14 statements (e.g., “I’ve been feeling confident.”) during the past two weeks. Answers are recorded on a five-point scale ranging from 1 “none of the time” to 5 “all of the time”. Reliability and validity of the WEMWBS has been confirmed in a German speaking sample (Lang & Bachinger, 2017).

#### Activity Data

##### Activity Ratings

To assess individual differences and changes in reward anticipation and motivation, participants in the Imagery BA condition will be asked to provide ratings of the following items pre and post intervention, that is, before and after the imagery-enhanced activity scheduling procedure: (a) how pleasant they expect the activity to be, (b) how rewarding they expect the activity to be, and (c) how motivated they are to engage in the activity. To control for potential differences in activity characteristics, ratings of activity importance, procrastination tendency, and previous engagement with the activity will be obtained pre intervention. As a manipulation check, allowing to infer whether participants succeeded in generating mental imagery, participants in the Imagery BA condition will rate mental imagery vividness and anticipatory pleasure (i.e., pleasure experienced while imagining the activity) post intervention.

##### Activity Monitoring Forms

To track whether and how participants engage in (scheduled) activities, they are asked to fill out activity monitoring forms in the week between Sessions 1 and 2, as well as in Sessions 3 and 4. In these forms, participants indicate which activities they engaged in (week after Session 1) or whether they engaged in their scheduled activities (Sessions 3 and 4). While inviting participants to fill out the activity monitoring form during the week, as implemented between Sessions 1 and 2, more closely matches standard BA procedures, where activity monitoring is typically given as a homework assignment, it was decided to deviate from this procedure after Session 2 to avoid confounding behavioral intervention effects with the potential reminder effect of activity monitoring invite messages sent in between sessions. For each activity, participants note the duration of their engagement in the activity, how enjoyable/rewarding they experienced the activity to be, and to what extent the activity influenced their mood. In case of non-engagement, participants can note a putative reason for this. The activity monitoring form is presented online and uses an interactive format that adapts to participants’ answers by displaying only relevant elements (e.g., depending on the initial answer whether or not participants engaged in a given activity).

#### Potential Moderators

##### Avoidance Tendencies

Avoidance tendencies will be measured from baseline to Session 4 using the Cognitive Behavioral Avoidance Scale (CBAS; Ottenbreit & Dobson, 2004; German version: Röthlin et al., 2010). In the CBAS, respondents rate appropriateness of 31 statements (e.g., “I quit activities that challenge me too much.”) on a five-point scale ranging from 1 “not at all true for me” to 5 “extremely true for me”. Excellent internal consistency of α = 0.92 has been reported for the German version (Röthlin et al., 2010).

##### The Ability to Generate Reward Imagery

The ability to generate reward imagery will be measured at baseline and Session 4 using the Freiburg Reward Imagery Scale (FRIS), a newly developed scale assessing individual differences in the ability to generate mental imagery of future activities including the associated positive emotional outcomes (for details, see pre-registration at https://osf.io/9y64q). For this scale, respondents are instructed to imagine engaging in a rewarding activity and subsequently rate the resulting mental image (subscales include vividness, anticipatory pleasure, anticipated pleasure, and motivation). Respondents rate their agreement with 12 statements (e.g., “This activity would make me happy.”) on an eleven-point scale ranging from 0 “not at all” to 10 “completely”.

##### Everyday Imagery Use

Everyday imagery use will be measured at baseline using the Spontaneous Use of Imagery Scale (SUIS; Kosslyn et al., 1998; German version: Görgen et al., 2016). In the SUIS, respondents rate the appropriateness of 12 statements (e.g., “When I think about visiting a relative, I almost always have a clear mental picture of him or her.”) on a five-point scale ranging from 1 “never appropriate” to 5 “always completely appropriate”. Acceptable (α = 0.72 - 0.76; Nelis et al., 2014) to good (α = 0.83; McCarthy-Jones et al., 2012) reliability has been reported for the English version. For the German version, Cronbach’s alpha has been reported to be lower (α = 0.66 in both studies; Görgen et al., 2016; Heise et al., 2022).

##### Symptoms of Anhedonia

Symptoms of anhedonia will be measured at baseline using the Temporal Experience of Pleasure Scale (TEPS; Gard et al., 2006). In the TEPS, anhedonia is assessed as two subcomponents, namely anticipatory pleasure (10 items, e.g. “Looking forward to a pleasurable experience is in itself pleasurable.”) and consummatory pleasure (8 items, e.g. “I really enjoy the feeling of a good yawn.”). Respondents rate agreement with items on a six-point scale ranging from 1 “very false for me” to 6 “very true for me”. Acceptable reliability indices for the anticipatory (α = 0.74 – 0.81) and consummatory (α = 0.69 – 0.74) subscales have been reported (Ho et al., 2015).

### Statistical Analyses

We will regard *p*-values less than .05 as criteria for statistically significant results. All reported *p*-values will be two-tailed.

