**Method:**

We describe a randomized controlled trial testing a mental imagery activity scheduling training delivered online in four weekly sessions (total training duration approximately 90 minutes) in a sample meeting diagnostic criteria of a major depressive episode, as indicated by the Diagnostic Short-Interview for Mental Disorders (Mini-DIPS), and not currently receiving treatment. Participants (N = 140) will be randomized to either mental imagery activity scheduling or a wait-list control condition. Depressive symptoms (BDI-II) and behavioral activation (BADS) are the primary outcomes; BDI-II will be measured at Session 1, Session 4, and at two-week follow-up, BADS at Sessions 1-4 and at two-week follow-up.

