### Participants

Inclusion criteria are (a) meeting the diagnostic criteria for a current major depressive disorder (MDD) as indicated by the Diagnostic Short-Interview for Mental Disorders (Mini-DIPS; Margraf et al., 2017), (b) a BDI-II score ≥ 14, indicating at least mild levels of depression, and (c) age between 18 and 65 years. Participants will be excluded if (1) they are currently in treatment for a mental health condition (psychotherapy and/or medication), (2) they present high levels of suicidality (as indicated by answers > 1 for item 9 of the BDI-II or the respective section in the Mini-DIPS), or (3) if they are meeting diagnostic criteria for one or more of the following disorders: bipolar disorder, psychotic disorders, or substance dependence.

*Sample Size.* Our aim is to obtain a dataset containing *n* = 140 complete observations, that is, with measurements for all four sessions and follow-up. This sample size was pre-registered (Heise et al., 2022S) and determined a priori using GPower (Faul et al., 2009). We assumed a small effect size (as observed in initial pilot testing), 95% Power, and α = 0.05. To account for attrition as observed in initial pilot testing, in which approximately 26% of baseline participants did not complete the follow-up assessment, we plan to recruit a total of *N* = 192 participants from the general population.

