#### Hypothesis 1 – Behavioral Activation

To test for differences between the Imagery BA condition and the wait-list control condition in change in behavioral activation across the five measurement points (Sessions 1–4, follow-up), we plan to conduct a repeated-measures ANOVA on the BADS score with condition (Imagery BA vs. wait-list control) as between-subject factor and time (Sessions 1–4, follow-up) as within-subject factor in an intention-to-treat analysis.

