#### Hypothesis 2 – Depressive Symptoms

To test for differences between the Imagery BA condition and the wait-list control condition in change in depressive symptoms across the three measurement points (Session 1, Session 4, follow-up), we plan to conduct a repeated-measures ANOVA on the BDI-II score with condition (Imagery BA vs. wait-list control) as between-subject factor and time (Session 1, Session 4, follow-up) as within-subject factor in an intention-to-treat analysis.

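### Two primary outcomes are each judged at two-tailed p < .05 with no rule linking them; if success on either may be claimed, the chance of a false primary claim is about 8 to 10%.

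*Protocol article*

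**What the plan says.** The abstract (Method) states that "Depressive symptoms (BDI-II) and behavioral activation (BADS) are the primary outcomes". Table 1 and the Measures section repeat this. The end of the introduction sets out two numbered expectations, one per outcome.

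Under Statistical Analyses, Hypothesis 1 is tested by a "repeated-measures ANOVA on the BADS score with condition (Imagery BA vs. wait-list control) as between-subject factor", with five time points. Hypothesis 2 is tested by a "repeated-measures ANOVA on the BDI-II score with condition (Imagery BA vs. wait-list control) as between-subject factor", with three. The criterion is set once for all results: p-values "less than .05 as criteria for statistically significant results", and all p-"values will be two-tailed".

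The sample size paragraph under Participants uses the same undivided level: "We assumed a small effect size (as observed in initial pilot testing), 95% Power, and α = 0.05". Its target is 140 "complete observations, that is, with measurements for all four sessions and follow-up", and 192 are to be recruited to allow for attrition.

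No section divides alpha, orders the two tests, or says whether one significant primary outcome is enough.

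**The concern.** Two tests at .05 give two chances of a false positive. If either may carry the primary conclusion, the chance that at least one is falsely significant exceeds .05, although each test on its own holds that level.

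The two outcomes also differ in kind. The Discussion treats depressive severity as the outcome and behavioral activation as the mechanism thought to drive it. BADS is a self-report of the behavior that the intervention trains, and the wait-list arm only fills in questionnaires. A trial that is positive on BADS and not on BDI-II is therefore a realistic result. The plan does not say whether that would be a positive trial. If this is settled after the data are seen, the choice of which outcome carries the claim cannot be defended.

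**Working it through.** **Inputs from the article.** Two primary outcomes; two-tailed p < .05 for each; 140 complete observations in two equal arms, so 70 per arm; five time points for BADS and three for BDI-II; 26% attrition; 95% power at α = 0.05. Both hypotheses concern differences in change, so I take the condition-by-time interaction as the test.

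**Inputs not in the article.** The correlation between the outcomes, the numerical effect size, and the correlation among repeated measures. These are assumed below and varied.

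**1. The plan's own figures.** 140 / (1 − 0.26) = 189.2, rounded up to 190, against the stated 192. Attrition of 27% gives 140 / 0.73 = 191.8, rounded up to 192. The 140 itself cannot be reproduced, because no effect size or repeated-measures correlation is given. With f = 0.1 and ρ = 0.5, the interaction test needs 188 (five time points) or 260 (three). About 140 results with f = 0.1 and ρ near 0.63 (five) or 0.73 (three). This does not show 140 to be wrong, and the error-rate argument does not depend on it.

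**2. Error rate, independent tests.** 1 − (1 − 0.05)² = 1 − 0.9025 = 0.0975. The upper bound under any dependence is 0.05 + 0.05 = 0.10.

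**3. Error rate, correlated tests.** For two-sided normal test statistics with correlation r, the rate is 1 − P(|Z₁| < 1.96 and |Z₂| < 1.96). As a check, both planned interaction tests were simulated with no true effect (70 per arm, 40,000 runs per value), with the assumed correlation placed between the two outcomes at each occasion.

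| Assumed correlation | Normal test statistics | Simulated ANOVA interactions |
|---|---|---|
| 0 | 9.75% | 9.5% |
| 0.3 | 9.5% | 9.6% |
| 0.5 | 9.1% | 9.4% |
| 0.7 | 8.35% | 9.0% |
| 0.8 | 7.8% | 8.5% |
| 0.9 | 7.0% | 8.1% |

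The correlation means something different in the two columns, so they need not agree row by row. The Monte Carlo standard error is about √(0.09 × 0.91 / 40,000) = 0.14 percentage points. In the simulation each single test stayed between 4.7% and 5.1%, so the excess comes from having two tests and not from a faulty one.

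**4. After a correction.** Each test at .025: 1 − 0.975² = 0.0494 if independent, and at most 0.05 under any dependence. Holm, a fixed sequence, or a both-must-succeed rule also keeps the rate at or below 5%.

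**5. Power at .025 with 140 complete.** Noncentral F with λ = f²·N·m / (1 − ρ) and degrees of freedom m − 1 and (N − 2)(m − 1), with f = 0.1 assumed:

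- m = 5, ρ = 0.65: λ = 0.01 × 140 × 5 / 0.35 = 20.0; power 96.3% at .05, 93.4% at .025.
- m = 3, ρ = 0.75: λ = 0.01 × 140 × 3 / 0.25 = 16.8; power 96.3% at .05, 93.4% at .025.
- m = 5, ρ = 0.5: λ = 14.0; 86.3% falls to 79.3%.
- m = 3, ρ = 0.5: λ = 8.4; 73.5% falls to 63.5%.

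The loss is about 3 points where power starts near the stated 95%, and larger where it starts lower.

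**The case against.** The strongest reply is that each hypothesis concerns a different construct. If each result is reported only as a claim about its own hypothesis, each claim carries a 5% error and nothing is inflated. The introduction also expects both effects together, which could be read as requiring both. This stands in part: the 8 to 10% applies only if success on either outcome may be presented as a positive primary result. But an expectation of both effects is not a decision rule, and two separately numbered and separately tested hypotheses leave the either-outcome reading open.

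A reader might go further and infer that the plan breaks a trial-wide 5% it had promised, or that it declares one significant outcome sufficient. The documents support neither. Statistical Analyses gives a criterion for each result, and the α in the sample size paragraph is an input to a power calculation. No family-wise rate is stated, and no success rule across the two outcomes is written.

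A second reply is that this is a condensed article, and the pre-registration it cites, or an analysis plan, may contain a multiplicity rule. That limits what can be said about the trial as a whole. It does not remove the point about the article, which itself fixes .05 for every result and sizes the trial at the same undivided level. A rule elsewhere that split or ordered alpha would have to override that text.

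**Conclusion.** The point holds in conditional form. With two primary tests each at two-tailed .05 and no linking rule, the chance of at least one false primary claim is about 8 to 10%, roughly 1.6 to 2 times .05. This assumes that both null hypotheses are true, that either success may be claimed, and that the outcomes have a low to fairly high correlation. That correlation is not in the documents. At 0.9 between the test statistics the rate would be 7.0%. If only one null hypothesis is true, the chance of a false claim on that outcome remains 5%.

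The defect is a stated criterion without a success rule, and it should be settled before the data are examined. It does not invalidate either ANOVA, and it does not show the sample size to be wrong.

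**What to change.** Add one rule to Statistical Analyses, for example: *The two primary condition-by-time tests (BADS, BDI-II) are evaluated with the Holm procedure at a family-wise two-sided error of .05: the smaller p-value against .025 and, if significant, the other against .05.*

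Two alternatives also hold 5%, and the choice depends on which claim is wanted:

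- **Fixed sequence, BDI-II first.** BADS is tested at .05 only if BDI-II is significant. This matches the Discussion's outcome-and-mechanism distinction and costs BDI-II no power. Unlike Holm, it does not allow a primary claim on BADS alone.
- **Both must be significant, each at .05.** This needs no adjustment, but the power that matters is joint. If each test has 95%, joint power is 0.95² = 90.25% for independent tests, and at least 1 − 0.05 − 0.05 = 90% in any case.

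Keep 140 complete and 192 recruited. Restate power from the sponsor's own effect size and repeated-measures correlation, at .025 for Holm's first step or as joint power for the third option. The article does not give these inputs, so the figure cannot be computed from it. The cost is a sentence and a lower stated power: about 3 points under Holm's first step where power starts near 95 to 96%, and more if the sponsor's inputs imply a lower start.
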